#### Secondary Outcomes

Diagnostic accuracy of inflammometry assessed through receiver operating characteristic (ROC) curve analyses using FeNO levels, BEC and their combined values, with BPT as gold standard. Clinically relevant thresholds will be identified to optimise rule-in capacity for asthma diagnosis in primary care, targeting ≥90% of specificity and a positive likelihood ratio (LR+) ≥10 in children, adolescents and adults (as three distinct subgroups).Assessment of inflammatory status on asthma control, evaluated pre-diagnosis and post-diagnosis using the ACQ-5, ACT and EQ-5D-5L questionnaire scores. Additional measures include the number of exacerbations, prescribed and dispensed medications and the frequency of specialised asthma consultations collected from clinical records, drug claims and patient electronic reports at baseline and at 4-month, 8-month and 12-month follow-up.Assessment of health benefits in terms of QALY, budget impact and economic efficiency (evaluated using incremental cost-effectiveness ratio (ICER) and Incremental cost-utility ratio (ICUR)) of integrating inflammatory biomarkers into primary care asthma diagnosis.The evaluation of annualised carbon dioxide (CO2) emissions from inhalers dispensed to non-asthmatic individuals awaiting their diagnostic tests was done based on drug claims and Cascades Canada environmental data.^27^ Environmental sustainability assessment of biomarker-enabled pathways will be explored.Descriptive analysis of patient satisfaction regarding inflammometry and the overall experience of diagnostic procedures, with responses stratified by age (6–<12, 12–<18, ≥18) and diagnostic test (BDR or BPT) and final asthma diagnosis status.

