For the primary outcome of waiting time differences, the baseline diagnostic delay, prior to the project implementation, will be established based on the time elapsed between the initial request for an asthma diagnostic test made by primary care and the performance of that test. During the intervention, diagnostic delays will be monitored prospectively, both overall and stratified by inflammatory status. We will apply linear mixed-effects models with restricted maximum likelihood estimation. These models will incorporate (high-risk vs low-risk), study period at time of inclusion, and the number of awaiting tests as fixed effects. Random effects will account for within-centre clustering and repeated measurements. In addition, Kaplan-Meier survival curves will be constructed to visualise the probability of remaining undiagnosed over time for both high-risk and low-risk inflammatory phenotypes. These curves will allow for a graphical representation of differences in diagnostic efficiency between groups. Cox proportional hazards regression will be used to identify significant predictors of waiting time with HRs and 95% CIs reported.

Diagnostic performance in the secondary outcome will be evaluated through ROC analysis, calculating the area under the curve (AUC) with 95% CIs for each individual marker and for their combined use. Sensitivity, specificity, positive and negative predictive values and likelihood ratios will be calculated with their respective 95% CIs.

Health utility values will be derived from EQ-5D questionnaires^39 52 53^ completed at baseline and follow-up visits. Quality-adjusted life years will be calculated using the AUC method, connecting utility values across measurement time points. This approach integrates health-related quality of life over the 12-month follow-up period. To assess the financial implications of implementing FeNO testing within the provincial healthcare framework, we will develop a budget impact model for the MSSS. Environmental and satisfaction-related outcomes will be analysed using descriptive statistics. CO₂ emissions from inhalers dispensed to non-asthmatic individuals will be estimated based on Cascades Canada data,^27^ and patient satisfaction with inflammometry will be assessed using structured questionnaires.

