### Discussion

This study addresses a critical gap in the literature by prospectively evaluating the implementation of inflammatory biomarkers in a real-world primary care referral pathway across both adult and paediatric populations. Beyond its scientific contribution, our protocol will optimise clinical resources by reducing the backlog of approximately 3000 respiratory function tests, currently awaiting completion across the three participating centres, through the engagement of study-dedicated respiratory therapists.

We anticipate that this study will demonstrate the utility of inflammatory biomarkers as effective triage and prioritise instruments for BPT. Given the high rate of false positives in respiratory testing as well as the substantial rate of clinical misclassification in Canada (between 33% and 45% in adults and children),^20 22^ our study will calculate optimal biomarker thresholds to achieve 90% specificity, positive predictive value (PPV) exceeding 80% and LR+ greater than 10—parameters essential for reliable diagnostic confirmation.^57^ In effect, this strategy sacrifices sensitivity in favour of specificity, leading to high PPV and LR+.

Existing literature supports the relevance of our approach. Li *et al* conducted a large retrospective cohort study involving 7463 adult patients with suspected asthma in secondary care. Among the 2349 patients with complete biomarker data, concurrent elevation of FeNO (> 40 ppb) and BEC (>0.3×10ˆ9 cells/L) was associated with a diagnostic specificity greater than 95%.^58^ Similarly, Nekoee *et al* demonstrated that combining biomarkers with spirometry improved diagnostic accuracy (AUC 0.82, 95% CI 0.78 to 0.86),^59^ reinforcing the relevance of inflammometry in routine assessment. Additionally, the predictive value of both BEC and FeNO has been demonstrated in adults,^812 15 16 19 60^,^70^ and to a lesser extent in the paediatric^50^ populations, with significant clinical implications for early intervention and treatment adjustment. Furthermore, these biomarkers are valuable tools for therapeutic decision-making, as elevated values are associated with a better response to anti-inflammatory therapies.^71^,^75^ As modifiable indicators, the inflammatory signals provided by BEC and FeNO highlight the importance of early measurement to better prioritise patients requiring timely inflammation control.^15 61 62 64^

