## Conclusion

This innovative multicentre observational study is the first to assess the real-world application of inflammatory biomarkers in the asthma diagnostic test pathway among both paediatric and adult populations referred from primary care. By prospectively evaluating FeNO and BEC and comparing with conventional lung function tests, we aim to inform a more efficient and evidence-based system for prioritising suspected asthma cases.

Biomarker-guided stratification appears promising to reduce diagnostic delays in patients with inflammatory phenotypes, thus minimising unnecessary treatment in non-asthmatic individuals and improving clinical outcomes through recommendations for targeted interventions. The study will provide solid evidence to refine age-specific biomarker cut-offs for diagnostic purposes, addressing the current scarcity of validated thresholds in the paediatric population and improving understanding of biomarker performance across diverse demographic groups.

By enhancing diagnostic accuracy and resource efficiency while supporting personalised care, this project will advance the principles of precision medicine. It integrates accessible biomarker tools into routine clinical practice, offering a scalable strategy to streamline diagnosis, control healthcare costs, potentially reduce the environmental impact of unnecessary inhalers used during diagnostic delays and foster a more sustainable and cost-effective approach to respiratory care.

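### Rule-in cut-offs are searched for and reported in the same age subgroup against an LR+ ≥10 target with no precision or sensitivity condition, so the LR+ at the chosen cut-off is biased upward

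*Protocol article*

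**What the plan says.** The first secondary outcome uses ROC "curve analyses using FeNO levels, BEC and their combined values, with BPT as gold standard". The cut-offs come from the study data: "Clinically relevant thresholds will be identified to optimise rule-in capacity for asthma diagnosis in primary care, targeting ≥90% of specificity". The same sentence sets LR+ ≥10 as a second target, to be pursued separately in each of three age groups. Three markers in three age groups make nine searches.

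The Discussion restates the aim and adds a predictive-value target: "our study will calculate optimal biomarker thresholds to achieve 90% specificity, positive predictive value (PPV) exceeding 80% and LR+ greater than 10". It accepts the price openly: "this strategy sacrifices sensitivity in favour of specificity, leading to high PPV and LR"+.

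Statistical methods then says: "Sensitivity, specificity, positive and negative predictive values and likelihood ratios will be calculated with their respective 95% CIs". The Conclusion states: "The study will provide solid evidence to refine age-specific biomarker cut-offs for diagnostic purposes". The Sample size section adds that the findings will feed a meta-analysis of diagnostic performance.

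None of these sections attaches a lower confidence limit, a minimum sensitivity or a minimum number of false positives to the target. None describes a correction for the search.

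**The concern.** A cut-off picked because its observed LR+ is at least 10, and then described by that same LR+, is subject to selection bias. The bias is worst where few non-asthmatic patients lie above the cut-off, and the LR+ target pushes the search there. Above the highest value in any non-asthmatic patient, observed specificity is 100% and LR+ is infinite, whatever the marker is truly worth.

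The cut-offs are meant for ruling in asthma in primary care and are presented as a main product of the study. An inflated LR+ would carry into that use and into the meta-analysis, and small subgroups would tend to give the most flattering figures.

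**Working it through.** **The plan's own ROC figure.** The only ROC sizing given is for DIVE/DIVE2: 123 participants at 2:1 (82 with asthma, 41 without), AUC 0.7 against 0.5, two-sided alpha 0.016, 90% power. The Hanley-McNeil variance is [A(1−A) + (n1−1)(Q1−A²) + (n0−1)(Q2−A²)]/(n1·n0), with Q1 = A/(2−A) and Q2 = 2A²/(1+A).
- At A = 0.7: (0.21 + 81×0.0485 + 40×0.0865)/3362 = 0.00226, SE 0.0475.
- At A = 0.5: (0.25 + 81×0.0833 + 40×0.0833)/3362 = 0.00307, SE 0.0554.
- Power = Φ[(0.2 − 2.409×0.0554)/0.0475] = Φ(1.40), about 92%.

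The stated size therefore reproduces. It concerns an AUC differing from 0.5, not a rule-in cut-off.

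**Which target binds.** LR+ = sensitivity/(1 − specificity), so LR+ ≥10 requires sensitivity ≥ 10 × (1 − specificity):
- specificity 90%: 100%
- specificity 95%: 50%
- specificity 98%: 20%

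**Simulation of the search.** The document gives no subgroup sizes, prevalence, marker distribution or selection algorithm, so all are assumed. AUC 0.70 and 67% asthma are borrowed from the DIVE sizing. Markers are normal in each group. A cut-off qualifies if observed specificity is ≥90% and LR+ ≥10. The lowest qualifying cut-off is taken, with at least 5 true positives except in the rows marked *. Observed LR+ is then compared with the true LR+ at that cut-off.

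| Assumed marker | Subgroup size | Cut-off found | Median apparent LR+ | Median true LR+ | Ratio |
|---|---|---|---|---|---|
| AUC 0.70, equal SD | 100 | 63–67% | infinite | 4.1 | infinite |
| AUC 0.70, equal SD | 400 | 77–78% | 16.3–17.7 | 5.2–5.3 | 3.1 or more |
| AUC 0.75, equal SD | 200 | 85–87% | 14.8–15.3 | 6.0–6.1 | 2.4–2.5 |
| AUC 0.80, equal SD* | 300 (200/100) | 99.5% | 11.5 | 8.2 | 1.4 |
| AUC 0.80, equal SD* | 600 (300/300) | 99.7% | 10.6 | 9.1 | 1.2 |
| AUC 0.70, SD ratio 1.25 | 400 | nearly all | 12.0 | 8.3 | 1.4 |
| AUC 0.70, SD ratio 1.5 | 400 | nearly all | 11.2 | 9.3 | 1.2 |

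The SD ratio is asthmatic to non-asthmatic. Among runs that met the target, the true LR+ was ≥10 in essentially none at AUC 0.70 with equal SDs, and in 29–43% with AUC 0.8 or SD ratios of 1.25–1.5.

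**Effect of a sensitivity floor** (equal SDs, several case/non-case splits, no true-positive minimum):
- No floor: an uninformative marker (AUC 0.5) met the target in 34–68% of runs, mostly with no false positives.
- 10% floor: this fell to 0–2%. At AUC 0.7 the target was still met in 15–44% of runs, with median true LR+ 3.7–4.6.

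**Which part of the target carries the bias.**
- Targeting specificity ≥90% alone gave apparent specificity 90.0–90.2% against true 88.6–90.0%. LR+ was, for example, 3.05 apparent against 2.96 true (67/133, AUC 0.7).
- A lower limit on specificity therefore screens poorly. At AUC 0.70 and 400 patients, all falsely qualifying cut-offs passed an uncorrected lower limit of 90%. With 0 false positives among 41 non-cases, the exact lower limit is already 0.025^(1/41) = 91.4%.
- The uncorrected lower 95% limit of LR+ reached 10 in none of the equal-SD runs (AUC 0.5 to 0.8).

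**The case against.** **The article states an aim, not an algorithm, and the SAP is not shown.** Internal validation may be specified there, so a reader who infers that none is planned goes beyond the document. This stands, and no omission is charged. What remains is that the article itself fixes a numerical target with no precision or sensitivity condition. That target needs a decision rule even if validation is specified elsewhere.

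**The size depends on the model.** A reader might infer that the published thresholds will look far better than they are, or that no true LR+ of 10 exists. At AUC 0.70 with equal variances, a true LR+ of 10 exists only at sensitivity 0.7%. With SD ratios of 1.25 and 1.5 it exists at 13.7% and 24.9%, and at AUC 0.8 with equal variances at 18.6%. The document does not settle which applies. AUC 0.7 is a lower bound taken from the sub-study sizing, and the Discussion cites an AUC of 0.82 for biomarkers combined with spirometry. So the stronger reading is not supported. The direction of the bias survived every variation tried.

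**95% CIs for likelihood ratios are planned.** They would show much of the imprecision, and a careful reader would see that LR+ ≥10 is not established. This stands, but nothing in the plan makes them decide whether a threshold is declared.

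**Conclusion.** The concern holds in limited form. A cut-off search in each age group against LR+ ≥10, with accuracy reported in the same patients and no sensitivity or precision condition, gives an upward-biased LR+.

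Under the assumed binormal models, the inflation is about 1.2-fold with AUC 0.8 in subgroups near 600, or an SD ratio of 1.5 in 400. It is about 1.4-fold with AUC 0.8 in 300 or an SD ratio of 1.25 in 400, and 3-fold or more at AUC 0.70 with equal variances. It is unbounded when there are no false positives. In every scenario tried, most qualifying cut-offs had a true LR+ below 10.

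The specificity target alone carries at most about 1.6 points of optimism. Subgroup sizes, prevalence, AUC, variance ratio and selection algorithm are all assumptions. The nine searches are correlated, so no joint probability of a chance success is given. The plan should be changed, but this affects a secondary outcome and leaves the primary comparison untouched.

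**What to change.** In Secondary Outcomes and Statistical methods:

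1. Repeat the whole cut-off search within bootstrap resamples, separately by age group, and report optimism-corrected sensitivity, specificity and LR+. Leave-one-centre-out would not work for adults, because Statistical methods describes two of the three centres as paediatric-only.
2. State in advance a minimum sensitivity, and a minimum false-positive count below which LR+ is reported as not estimable.
3. Claim that LR+ ≥10 is met only if the lower 95% limit of the corrected LR+ supports it. Otherwise report the cut-off at fixed 90% specificity, with its LR+ labelled exploratory. A lower limit on specificity should not be the gate.
4. Temper the Conclusion's description of the evidence for age-specific cut-offs.

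This costs R code and wording, with no new data. Reported accuracy will be less favourable, and some or all subgroups may yield no threshold with LR+ ≥10.

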### Translational outcomes

Evaluation of the association between inflammatory biomarkers and underlying inflammatory mediators through participation in the DIVE and DIVE2 translational sub-studies. Findings will be linked to the final asthma diagnosis. The remaining biobanked samples will serve future translational analyses for biomarker discovery in asthma diagnosis, for example, based on epigenetic or metabolomic signatures.

### Statistical methods

Data will be independently analysed by a biostatistician from the CHUS using R software (V. 4.2.0 or later, R Foundation for Statistical Computing, Vienna, Austria) in collaboration with a health economist. Missing data will be documented, and multiple imputation by chained equations will be considered for data missing at random when <20% of data is missing. Statistical significance will be determined using a two-sided alpha level of 0.05. Adjustments for multiple comparisons with the Benjamini-Hochberg procedure will be applied where necessary, including for subgroup analyses on the primary outcome.^51^

All primary analyses will also be stratified by pre-specified subgroups: study site, age categories (6–<12 years, 12–<18 years, ≥18 years), biological sex, ethnicity, smoking status and other potential confounding variables related to inflammatory biomarker measurement. Additionally, we will perform sensitivity analyses excluding active smokers. Categorical variables will be presented as counts with corresponding percentages, while continuous variables will be reported as either means with standard deviations (for normally distributed data) or medians with interquartile ranges (for non-normally distributed data). For comparative analyses between groups, we will employ independent t-tests or Mann-Whitney U-tests for continuous variables based on distribution, and χ^2^ tests or Fisher’s exact tests for categorical variables, as appropriate based on expected cell frequencies.

For the primary outcome of waiting time differences, the baseline diagnostic delay, prior to the project implementation, will be established based on the time elapsed between the initial request for an asthma diagnostic test made by primary care and the performance of that test. During the intervention, diagnostic delays will be monitored prospectively, both overall and stratified by inflammatory status. We will apply linear mixed-effects models with restricted maximum likelihood estimation. These models will incorporate (high-risk vs low-risk), study period at time of inclusion, and the number of awaiting tests as fixed effects. Random effects will account for within-centre clustering and repeated measurements. In addition, Kaplan-Meier survival curves will be constructed to visualise the probability of remaining undiagnosed over time for both high-risk and low-risk inflammatory phenotypes. These curves will allow for a graphical representation of differences in diagnostic efficiency between groups. Cox proportional hazards regression will be used to identify significant predictors of waiting time with HRs and 95% CIs reported.

Diagnostic performance in the secondary outcome will be evaluated through ROC analysis, calculating the area under the curve (AUC) with 95% CIs for each individual marker and for their combined use. Sensitivity, specificity, positive and negative predictive values and likelihood ratios will be calculated with their respective 95% CIs.

Health utility values will be derived from EQ-5D questionnaires^39 52 53^ completed at baseline and follow-up visits. Quality-adjusted life years will be calculated using the AUC method, connecting utility values across measurement time points. This approach integrates health-related quality of life over the 12-month follow-up period. To assess the financial implications of implementing FeNO testing within the provincial healthcare framework, we will develop a budget impact model for the MSSS. Environmental and satisfaction-related outcomes will be analysed using descriptive statistics. CO₂ emissions from inhalers dispensed to non-asthmatic individuals will be estimated based on Cascades Canada data,^27^ and patient satisfaction with inflammometry will be assessed using structured questionnaires.

Additional exploratory clinical outcomes will be analysed using appropriate descriptive statistics in accordance with distribution. Linear and logistic regression analyses will associate the diagnostic outcome, T2 biomarkers and blood/NELF inflammatory mediators.

Sensitivity analyses will be conducted with the exclusion of paediatric-only study sites (CHUSJ and MCH-MUHC) and with different diagnostic asthma criteria (eg, BDR with 10% in % predicted FEV1 or FVC values, BPT with PD20 <200 µg).

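### Subgroup results on diagnostic delay rest on stratified, Benjamini-Hochberg-adjusted tests with no interaction test named, and the primary mixed model leaves out age category

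*Protocol article*

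**What the plan says.** All of this is in the protocol article, under Statistical methods unless stated otherwise.

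- **Subgroups.** "All primary analyses will also be stratified by pre-specified subgroups". The list is study site, three age categories, "biological sex, ethnicity, smoking status and other potential confounding variables related to inflammatory biomarker measurement".
- **Error control.** Tests are two-sided at the 5% level. On multiplicity the article says: "Adjustments for multiple comparisons with the Benjamini-Hochberg procedure will be applied where necessary, including for subgroup analyses on the primary outcome". No interaction between risk class and subgroup is mentioned.
- **Primary model.** A linear mixed model is planned: "These models will incorporate (high-risk vs low-risk), study period at time of inclusion, and the number of awaiting tests as fixed effects". Centre and repeated measures are handled through random terms. The Primary Outcome section likewise names only time of inclusion as an adjustment.
- **Other handling of the same variables.** For smoking, "we will perform sensitivity analyses excluding active smokers". A further sensitivity analysis drops the two paediatric-only sites. A Cox model for predictors of waiting time is planned, with its covariates not named.
- **Role of age.** The Abstract and the Intervention section set the FeNO cut-off at 25 ppb from age 12 and 20 ppb below it. Age, sex and smoking status are recorded at the study visit (Study visits).

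**The concern.** There are two separate points.

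**Subgroups.** Adjusted p-values within strata answer whether delay differs by risk class in a given stratum. They do not answer whether the difference varies between strata. Where one stratum passes the threshold and its neighbour does not, the natural reading is that prioritisation works for one group and not the other, and that pattern is common when the effect is uniform. The Conclusion section expects the study to inform biomarker performance across demographic groups, so such contrasts will attract attention.

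**Age in the pooled contrast.** Risk class is observed, not randomised, and its definition changes at age 12. If age also relates to waiting time, through separate queues or otherwise, the pooled high-risk versus low-risk difference mixes the pathway's effect with a difference in age mix. Stratifying by age removes this between age categories in the stratified tables, but not in the pooled estimate that the mixed model delivers.

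**Working it through.** **1. The plan's own figure.** The Sample size section gives a detectable Cohen's f of 0.07 with N = 1500, 80% power, alpha 5% and correlation 0.5, for the between-subjects factor of a repeated-measures ANOVA. The numbers of groups (k) and measurements (m) are not stated. Using a noncentral F with lambda = f² × N × m / (1 + (m − 1) × 0.5), the detectable f is 0.0724 for k = 2, m = 1; 0.0695 for k = 3, m = 2; and 0.0697 for k = 4, m = 3. The stated 0.07 is therefore attainable, and this point does not dispute it. For two equal groups it corresponds to d = 2 × 0.07 = 0.14.

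**2. Chance of a mixed pattern under a uniform effect, unadjusted tests.** Assume equal risk groups of 750 and one measurement each. The standard error is sqrt(2/750) = 0.0516 SD. At exactly 80% power the expected z is 1.96 + 0.84 = 2.80, so d = 2.80 × 0.0516 = 0.145. In each of g equal strata the expected z is 2.80/√g.

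| g | expected z | power per stratum | P(some but not all significant) |
|---|---|---|---|
| 2 | 1.98 | 0.508 | 2 × 0.508 × 0.492 = 0.50 |
| 3 | 1.62 | 0.366 | 1 − 0.366³ − 0.634³ = 0.70 |

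With a larger effect the chance drops. At d = 0.30 it is about 3% for two strata and 22% for three; at d = 0.50 both are below 0.1%.

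**3. The same question with Benjamini-Hochberg applied.** This is a simulation of 4000 runs with N = 1500 and a normal outcome. It uses 12 strata from five independent factors, with assumed splits: site 50/25/25, age 25/25/50, sex 50/50, ethnicity 80/20, smoking 85/15.

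| Uniform d | At least one factor with some but not all strata significant | False subgroup difference, interaction tests under Benjamini-Hochberg |
|---|---|---|
| 0 | 4% | 5% |
| 0.145 | 66% | 5% |
| 0.20 | 89% | 5% |
| 0.30 | 71% | 6% |

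Benjamini-Hochberg does its job when there is no effect at all (4%). It gives no protection against mixed patterns once a uniform effect exists, because those patterns are not what it controls. Five unadjusted interaction tests would give a false difference in about 23%.

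**4. What interaction tests can find.** For two equal halves the standard error of the interaction is twice that of the main effect. An interaction as large as the main effect then has expected z = 2.80/2 = 1.40 and power of about 29%.

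**5. Confounding by age.** The document gives neither waits nor risk-class prevalence by age, so any size is an assumption. Suppose adults and children are equal in number, wait 14 and 8 months, and are high-risk in 45% and 60% of cases, with no true effect:

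- High-risk mean: (0.45 × 14 + 0.60 × 8)/1.05 = 10.57 months.
- Low-risk mean: (0.55 × 14 + 0.40 × 8)/0.95 = 11.47 months.
- Spurious difference: −0.90 months.

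That crude contrast ignores the centre effect. With the same inputs, a within-centre contrast and all 750 adults at the one site that is not paediatric-only, the bias depends on how many of the 750 children attend that site:

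| Children at that site | Bias, months |
|---|---|
| 0 | 0 |
| 75 | 0.17 |
| 150 | 0.31 |
| 250 | 0.46 |

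These figures do not allow for differences between under-12s and adolescents inside the paediatric sites. The FeNO cut-off changes there too, and a centre effect cannot correct it.

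**The case against.** The strongest reply is that this is an article, and that interaction terms and reporting rules belong in an analysis plan that is not shown. The text never says that strata will be compared by their significance. That is fair as to reporting, and a reader should not infer that the study will announce spurious age- or sex-specific benefit; the document describes no such claim. But the article does more than stay silent. It chooses stratification, chooses the p-value correction for it, and lists the model's fixed effects, so those choices can be assessed.

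A reader might also infer that age and smoking are handled by stratification alone. They are not. Active smokers and the paediatric-only sites are each removed in a sensitivity analysis, centre is a random effect, the number of awaiting tests may capture some queue differences, and the Cox model may include either variable. These measures stand as partial safeguards. None of the stated ones adjusts the pooled mixed-model estimate for age within a site.

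It is likewise tempting to treat every variable on the stratification list as a confounder of delay. The text ties the open-ended item to biomarker measurement, and the Introduction says provocation tests are scheduled chronologically, with priority only for internal referrals. Nothing links smoking, sex or inhaled corticosteroid use to queue position.

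Finally, the 50% and 70% figures are unadjusted and set at the smallest detectable effect. The pathway could produce a larger one, given prioritised tests within weeks against waits above a year. That objection stands for equal strata. It is weaker for small, unequal strata, as the simulation shows.

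**Conclusion.** The point holds in limited form. As written, the subgroup method cannot show that strata differ, and a mixed pattern under a uniform effect is likely: about 50% for two equal strata and 70% for three, unadjusted and at exactly 80% overall power, and much lower for large effects. With Benjamini-Hochberg over 12 assumed strata it is 66% to 89% for uniform effects of 0.145 to 0.30 SD.

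The omission of age category leaves the pooled contrast open to confounding that the centre effect and the sensitivity analyses reduce but do not remove within a site. Its size cannot be established from the document. The 0.9-month figure is an illustration on assumed inputs that sets the centre effect aside, and it should not be quoted as an estimate. The document does not state that age relates to waiting time within a site; that is plausible but unproven. Confounding by smoking, sex or inhaled corticosteroid use is not supported.

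**What to change.** - Add age category as a fixed effect in the primary mixed model. Sex and smoking status can be added at little cost. Adjustment for inhaled corticosteroid use is optional, and the document gives no basis for requiring it.
- Test each subgroup factor by a risk class by subgroup interaction in that same model, and apply Benjamini-Hochberg across the interaction tests.
- Present stratum estimates with confidence intervals as descriptive, without stratum p-values.

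This is a change of plan wording; age, sex and smoking status are already collected. It uses a few degrees of freedom among about 1500 patients. Power for interactions is limited (about 29% for one as large as the main effect, equal halves), so a non-significant interaction should not be reported as evidence that the strata are alike.
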